### Study outcomes

The primary end points of EUC-CHF are the changes of weight loss and dyspnea severity score at every scheduled visit which are considered as the part of a single composite endpoint, as well as the occurrence of clinically major bleeding defined by TIMI or GUSTO criteria [12].

Secondary outcomes include: net fluid loss, length of stay in CCU or ICU, change of score by MLWHFQ functional capacity, change of serum and ultrafiltrate concentrations of endotoxin, ET-1, TNF-a, IL-6 and IL-10, changes of cardiac function (the NYHA classification), changes in N-terminal proB-type natriuretic peptide (NT-proBNP) level, changes of LDs dose, HF rehospitalizations for congestive HF in 30 days after discharge, cardiovascular death and all-cause death in 30 days after discharge, change of blood pressure, changes in hepatic and renal function (serum creatinine concentration, estimated glomerular filtration rate [eGFR]), serum electrolytes, hemoglobin and incidence of acute coronary syndrome at scheduled visits.

Weights will be obtained at every scheduled visit using the same balance with the patient shoeless in a hospital gown after emptying the bladder. Weight loss is the difference between weight at baseline and the weight recorded at subsequent visits.

The dyspnea severity score by a proposal to standardize dyspnea measurement in clinical trials of acute heart failure syndromes by International Working Group on acute heart failure of European Society of Cardiology is used for the assessment of dyspnea [13].

Total fluid intake and output (ultrafiltrate and urine) measured at every scheduled visit after enrollment will be used to calculate net fluid losses.

Glomerular filtration rate will be calculated according to the abbreviated Modification of Diet in Renal Disease (MDRD) equation [14].

Acute coronary syndrome includes unstable angina, ST segment elevated myocardial infarction and non-ST segment elevated myocardial infarction. Myocardial infarction is defined according to the fourth universal definition of myocardial infarction [15]. Death will be considered cardiac according to the 2014 ACC/AHA key data elements and definitions for cardiovascular endpoint events in clinical trials [16].

We also will collect all the urine output after patients are enrolled to receive standard medical therapy or early UF until 72 h after the end of study treatment. Then we will measure the average urine electrolytes for every enrolled patient.

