**Methods:**

The early continuous ultrafiltration in Chinese patients with congestive heart failure (EUC-CHF) trial is an open-label, registry-based, prospective study, recruiting patients with severe acute decompensated HF who are hospitalized for HF worsening due to overt fluid overload 24 h from hospital admission. Forty patients will be enrolled to two treatment groups (*n* = 20 for each group). The primary outcomes are the changes of weight loss and dyspnea severity score after treatment, as well as the occurrence of clinically overt major bleeding.

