**Fig. 1 Fig1:**
[figure not shown]
Study design. The control group will be treated with intravenous loop diuretics by experienced HF cardiologists according to guideline recommendations. Patients of the early UF group will receive a single or repeated session of UF started within 24 h from admission until the relief of patient’s symptom. HF, heart failure; UF, ultrafiltration

The trial aims to recruit 40 patients (20 patients for each group) over an estimated 24-month period. After baseline visit, follow-up visit will occur at the end of study treatment, 24 h, 48 h, and 72 h after the end of study treatment, at discharge, and 30 days after discharge. At the baseline visit, informed consent will be taken, and additional baseline variables including gender, age, height, weight, occupation, race, physical activity, complete medical history (including history of smoking and drinking, past and present medical history, concomitant disease), vital signs, NYHA classification, dyspnea severity score, score by Minnesota Living with Heart Failure Questionnaire (MLWHFQ) functional capacity, physical examination including distention of jugular vein, edema of lower extremity and congestion of other organs, laboratory test, electrocardiogram, chest X-ray, echocardiographic data and concomitant drug used up to 3 months before enrollment will be recorded.

Questionnaires (dyspnea severity score and score by MLWHFQ functional capacity) at follow-up visits will also be collected by trained clinicians. This will aid in our assessment of patients’ cardiac function and other safety data.

During follow-up, we will record all the primary and secondary end points and adverse events. All adverse events will be evaluated according to severity, causality, expectedness, and relationship to study treatment. Subjects who develop complications that, in the judgment of principal investigator or sub-investigator, are not suitable to continue the trial will be screened out from the study. Participants will continue with follow-up and may restart study protocol if the clinical situation resolves. Investigators are responsible for the decision to resume the study. If treatment according to the study protocol is clinically insufficient, the study will be suspended and effective treatment should be applied according to the current clinical practice.

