### Statistical analysis

We will compare estimates of patients who receive UF therapy with those who receive conventional pharmacologic therapy. Concomitant medication and other baseline characteristics will be utilized in subgroup analysis.

Continuous variables will be summarized using descriptive statistics. Qualitative variables will be summarized by counts and percentages.

We will compare baseline characteristics. T-test or sign rank test will be used after testing for normality. Chi-square or Fisher’s exact test will be performed for categorical variables.

The primary efficacy endpoint (change of weight loss and dyspnea severity score) will be analyzed by Kaplan-Meier method, and comparisons between two groups will be performed using a log-rank test. Hazard ratio with 95% CI will be derived by the Cox proportional hazards model. Subgroup analyses of the efficacy endpoint are performed for the evaluation of impact of major clinical features on the improvement of primary efficacy endpoints by early UF therapy. Specific information is as follows:

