The ability to predict the therapeutic effect of UF by patients’ individual characteristics as well as systolic blood pressure, heart rate, severity of edema, renal and hepatic function, NYHA classification, left ventricular ejection fraction, chamber diameter, concomitant disease and medication;The influence of different patients’ individual characteristics including gender, age, height and weight on the effect of UF for fluid removal and alleviation of dyspnea;The influence of baseline systolic blood pressure and heart rate on the effect of UF for fluid removal and alleviation of dyspnea;The influence of baseline severity of edema (i.e., edema of lower extremity and congestion of other organs) on the effect of UF for fluid removal and alleviation of dyspnea;The influence of baseline renal and hepatic function on the effect of UF for fluid removal and alleviation of dyspnea;The influence of different baseline cardiac function (including NYHA classification and left ventricular ejection fraction) on the effect of UF for fluid removal and alleviation of dyspnea;The influence of different baseline chamber diameter on the effect of UF for fluid removal and alleviation of dyspnea;The influence of different baseline concomitant disease on the effect of UF for fluid removal and alleviation of dyspnea;The influence of different concomitant medication on the effect of UF for fluid removal and alleviation of dyspnea;

Subgroup analysis of primary efficacy endpoint will be estimated using a stratified Cox model. The subgroup analysis will be tested by chi-square or Fisher’s exact tests.

The primary safety endpoints and secondary endpoints will be presented by summary statistics, as number of patients, event counts and percentage, variable counts and percentage.

All comparisons will report *p* values on the basis of 2-sided tests, and a p value ≤ 0.05 will be considered statistically significant. All statistical analyses will be performed using SPSS Statistics version 22 software.

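### The weight-and-dyspnea composite has no joining rule, event definition or deciding visit, so its time-to-event analysis cannot be run as written and the primary false-positive rate is not fixed

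*Protocol article*

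**What the plan says.** - **Study outcomes:** the primary efficacy end point is "the changes of weight loss and dyspnea severity score at every scheduled visit which are considered as the part of a single composite endpoint". Major bleeding is a further primary end point.
- **Abstract, Methods:** "The primary outcomes are the changes of weight loss and dyspnea severity score after treatment", in the plural and with no mention of a composite.
- **Study overview, text after Fig. 1:** "follow-up visit will occur at the end of study treatment, 24 h, 48 h, and 72 h after the end of study treatment", then "at discharge, and 30 days after discharge". That makes six post-baseline visits.
- **Statistical analysis, method:** "The primary efficacy endpoint (change of weight loss and dyspnea severity score) will be analyzed by Kaplan-Meier method", with a log-rank test between groups and a hazard ratio from a Cox model. No test by component or by visit is described. The end point is singular here but plural later in the same paragraph, and the subgroup list treats fluid removal and relief of dyspnea as two separate effects.
- **Statistical analysis, threshold:** for all comparisons, "a p value ≤ 0.05 will be considered statistically significant", with p "values on the basis of 2-sided tests". No multiplicity adjustment is mentioned. The primary safety end point is only to be summarised descriptively.

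**The concern.** Weight is measured in kilograms and dyspnea on a severity score. They become one end point only through a rule: both must improve, either may improve, or they are combined into a score. The article gives no such rule. It also sets no threshold that would turn a change into an event, and no visit at which the answer is read. A log-rank test compares times to an event, so the article prescribes an analysis for which the event does not yet exist.

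Someone will have to choose the event, the component and the visit later, in an open-label trial of 40 patients. If those choices are made after data are seen, the nominal 5% no longer describes the risk of a false primary claim. A claim resting on dyspnea alone at one favourable visit would be weak evidence, and the text as it stands does not prevent it.

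**Working it through.** **Step 1. Can the stated analysis be run?** Kaplan-Meier, log-rank and Cox methods each need an event and a time origin.

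| Needed | In the article |
|---|---|
| Event threshold for weight | not given |
| Event threshold for dyspnea | not given |
| Joining rule (both, either, score) | not given |
| Deciding visit, or first-attainment rule | not given; every scheduled visit is named |
| Time origin for the event | not given; the visits at 24, 48 and 72 h run from the end of study treatment |

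The analysis cannot be run until these are filled in.

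**Step 2. What false-positive rate follows from each way of filling them in?**

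Inputs from the article: two-sided 0.05 per comparison and 2 components (weight, dyspnea); 6 post-baseline visits; 20 patients per group. Bleeding is left out because no test of it is planned. The article states no overall error rate, so there is no figure of its own to reproduce.

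Assumed, because the article gives no values: correlation of 0.5 to 0.95 between visits and 0 to 0.7 between components.

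For k independent tests at 0.05, the chance of at least one false positive is 1 − 0.95^k.

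- (a) One defined event, one log-rank test: k = 1, giving 5.0%.
- (b) Each component tested once, either sufficing: k = 2, giving 1 − 0.95² = 9.75%.
- (c) Either component at any visit: k = 2 × 6 = 12, giving 1 − 0.95¹² = 46.0%.

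The tests in (b) and (c) are correlated, so both were also simulated under no treatment effect: 20 per arm, two-sided t-tests, 20,000 runs per setting. For (c) the between-visit correlation was either equal for all pairs or decayed with distance, AR(1). The t-test stands in for a by-visit comparison, since the article names only a log-rank test for this end point.

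- (b) 8.6 to 9.7% for component correlation 0.7 down to 0.
- (c) selected settings:

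| Visit correlation | Component correlation | Equal | AR(1) |
|---|---|---|---|
| 0.5 | 0 | 37.6% | 41.4% |
| 0.8 | 0.5 | 24.5% | 29.9% |
| 0.95 | 0.7 | 14.9% | 17.5% |

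Across all settings, (c) runs from about 15% to 41%; independence gives the upper figure of 46%.

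**Step 3. What would control the rate, and at what price?** The standardised difference detectable with 80% power at 20 per group is approximately (z for 1 − α/2, plus z for 0.80) × √(2/20).

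| Rule | α per test | False-positive rate | Detectable difference |
|---|---|---|---|
| One test, or first test of a fixed sequence | 0.05 | 5% | 0.89 SD |
| Two tests, α split | 0.025 | at most 5% (simulated 4.5 to 4.9%) | 0.97 SD |
| Twelve tests, α split | 0.05/12 = 0.0042 | at most 5% (simulated 1.6 to 4.8%) | 1.17 SD |

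A fixed sequence keeps the full 0.05 for its first test. The second is tried only after the first succeeds, so the two together stay within 5%.

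**The case against.** The strongest reply is that the Statistical analysis section names one end point, in the singular, and one log-rank test. On that reading the rate is 5%. The threshold sentence is general; it does not create twelve primary tests or say that any one of them is a win. This stands against a stronger conclusion that a reader might draw, namely that the primary false-positive rate simply is several times 5%. That would follow only if either component at any visit could be declared a success, and the article states no such rule. Twelve is also a maximum, since discharge has no fixed time and may coincide with another visit. The reply does not rescue the plan, though: the 5% depends on an event that has not been defined.

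A second reply is that event thresholds and multiplicity rules are commonly left to a full protocol or analysis plan, which is not shown and may settle them. That is fair for omitted detail. Here, however, the article itself asserts a composite, every visit, a method and a threshold, and these do not fit together.

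Third, the difference between abstract and body is modest. The scheduled visits begin at the end of treatment, so the abstract's wording can be read as shorthand. It adds to the ambiguity but is not a contradiction on its own.

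Finally, a reader might take dyspnea to be purely patient-reported. The article says only that trained clinicians collect the questionnaires, and it provides for blinded endpoint adjudication and a blinded statistician. Treatment itself is open-label, which is as far as the text goes.

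**Conclusion.** The point holds in a limited form. The composite lacks a joining rule, an event and a deciding visit, so the named time-to-event analysis cannot be executed as written. The primary error rate is therefore undetermined, not demonstrably inflated: one to about two times the nominal level under readings (a) and (b), and about three to nine times (15/5 to 46/5) only under the any-component, any-visit reading.

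That the rate is not fixed rests on the text alone. The simulated ranges rest on assumed correlations and on t-tests standing in for by-visit comparisons. All the rates also assume comparable groups, whereas the article describes sequential 1:1 enrolment and concedes possible selection bias. The sample size of 40 is not called wrong here; the article gives no inputs from which to check it. The matter should be corrected before any outcome comparison is made.

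**What to change.** 1. Drop the description as a single composite.
2. Name one primary comparison: the between-group difference in weight change, adjusted for baseline weight, at one pre-named time. That time can be an existing scheduled visit or one added weighing at a fixed time from enrolment. The 24, 48 and 72 h visits run from the end of study treatment, so 72 h from enrolment, for example, is not a visit in the current schedule. An existing visit needs no extra measurement, but its timing depends on how long treatment lasts; a time fixed from enrolment avoids that.
3. Test dyspnea at the same time only if weight is significant, each at 0.05.
4. Replace the Kaplan-Meier, log-rank and Cox wording for this end point with that analysis, and bring the subgroup wording that relies on a stratified Cox model into line.
5. Report the other visits as secondary, with 95% confidence intervals.
6. Leave major bleeding as the separate safety end point it already is.

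Putting weight first is a choice, not the only valid one. A single responder event with stated thresholds, a both-components rule, or 0.025 for each component would also control the error; splitting α raises the detectable difference from 0.89 to 0.97 SD.

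Cost: edits to the outcomes and statistics sections and a registry update, in a trial recruiting since December 2018. A time fixed from enrolment adds one weighing and one dyspnea score per patient. The main loss is that dyspnea alone no longer counts as a win.

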Currently, UF recommend by most of the guidelines are usually considered for patients with refractory congestion not responding to medical therapy. Previous research found although UF improve hemodynamics in acute decompensated HF refractory to standard medical therapy, it was also associated with high incidence of renal function damage and high in-hospital mortality [6]. However, other research found UF within 12 h of hospitalization in HF patients with volume overload and LD resistance before IV LDs effectively decreased length of stay and readmissions up to 3 months without change of renal function [7]. At present, most of the studies support UF should be considered as early treatment strategies (24 h after admission) in patients with severe HF instead of a “rescue therapy”. Early UF may prevent undesirable cardiorenal syndrome and sodium-volume overload before renal tubular damage induced by further neurohormonal activation and side effects caused by high dose LDs [8, 9].

Taken together, previous related studies showed UF is more effective in decongestion, haemodynamic variables and clinical outcome improvement, as well as restoring LD responsiveness compared with LDs. But most of the studies were based on the foreign population and did not define the exact time period from admission to UF. We do not have the related data for early UF in Chinese population. Furthermore, former study did not define how to screen out the patients recommended for early UF by specific scoring system. Our study aims to determine if early UF 24 h within admission in acute HF is superior to IV LDs in clinical parameter improvement without adverse events and prevents rehospitalization up to 30 days in Chinese population.

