### Study overview

The EUC-CHF trial is an open-label, registry-based, prospective, single center study. It will recruit patients with severe acute decompensated HF who are hospitalized for HF worsening and significant weight gain due to overt fluid overload 24 h from hospital admission. The determination that acute decompensated HF is the primary cause of hospitalization will be made by the site’s principal investigator or sub-investigator, based on the assessment of the clinical signs and symptoms as well as laboratory examinations that lead to the admission. Patient enrollment should be completed and study treatment initiated within 24 h from hospital admission. Patients will be enrolled 1:1 sequentially to receive standard medical therapy (control group) or early UF (early UF group). Up to 2 doses of IV LDs will be allowed before enrollment.

The diuretic protocol adopted by our study in the control group refers to the protocol of AVOID-HF and CARRESS-HF trial as well as the dose recommended by the guideline according to patients’ vital signs, status of hemoconcentration, and renal function (Table 1) [10, 11]. Patients of the early UF group will be treated with a single or repeated session of UF within 24 h from admission (according to local clinical practice and with availability of nursing surveillance during UF) until the relief of patient’s symptom. The UF protocol adopted by our study also refer to the protocol of AVOID-HF and CARRESS-HF trial (Table 2).

[figure not shown]

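### CCU/ICU stay as worded is shortened by a death in the unit, and the listed death outcome, worded from discharge, would not show that death

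*Protocol article*

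**What the plan says.** The secondary outcomes in the protocol article (Study outcomes) begin with "net fluid loss, length of stay in CCU or ICU". No start, end or death rule is attached to the stay, and it is not restricted to survivors or to patients who leave the unit alive.

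The same list gives mortality as "cardiovascular death and all-cause death in 30 days after discharge". No other listed outcome counts deaths.

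On analysis, the article says "The primary safety endpoints and secondary endpoints will be presented by summary statistics" (Statistical analysis). It names no competing-event, worst-rank or survivor-only approach.

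The direction of benefit is clear from context. The Background cites a study in which ultrafiltration (UF) within 12 hours reduced length of stay, and the Discussion lists shorter stay among the gains reported by the early-UF trials.

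**The concern.** Unit stay has a favourable direction (shorter), and death moves it that way. Someone who dies in the unit on day 2 records 2 days, and a survivor who needed 6 days records 6. On this outcome the death is the better result.

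Normally a reader would see the deaths in the mortality outcome beside it and discount the shorter stay. Here that outcome is worded to start at discharge. A patient who dies in the unit is never discharged, so on a literal reading the death shortens the stay and is counted in neither of these two outcomes.

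The population is sick enough for this to matter: severe acute decompensated heart failure, NYHA III-IV. Balance in early deaths cannot be taken for granted with 20 patients per arm. The allocation is described as "Patients will be enrolled 1:1 sequentially to receive standard medical therapy" or early UF, and the Discussion itself says selection bias cannot be excluded.

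**Working it through.** The article gives no mean or SD for unit stay and no in-hospital death rate, so there is no figure of its own to reproduce. From the article: 20 patients per arm, and a two-sided significance level of 0.05. Everything else below is an assumption.

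**1. Shift in an arm's mean stay.** If *k* of 20 patients die in the unit at day *d* and would otherwise have stayed *m* days, the observed mean falls by *k*(*m* − *d*)/20.

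| Assumed *m*, *d* (days) | 1 death | 2 deaths |
|---|---|---|
| 6, 2.5 | 3.5/20 = 0.175 | 0.35 |
| 10, 2.5 | 7.5/20 = 0.375 | 0.75 |
| 4, 2 (low end) | 2/20 = 0.10 | 0.20 |
| 10, 1 (high end) | 9/20 = 0.45 | 0.90 |

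Three deaths give 0.30 to 1.35 days over the wider range. The direction is always the same.

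**2. Size against noise.** With an assumed SD of 4 days, the standard error of a difference in means is 4 × √(2/20) = 1.26 days. A shift of 0.175 to 0.75 day is 0.14 to 0.59 of that. With 20 per arm, the difference detectable with 80% power is (1.960 + 0.842) × √(2/20) = 0.89 SD, or about 3.5 days at that SD.

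**3. Are unit deaths likely at all?** The chance of at least one in-hospital death among all 40 patients is 1 − (1 − *p*)^40: 55%, 70%, 87% and 99% for assumed *p* of 2%, 3%, 5% and 10%. This shows only that the question will probably arise. It does not measure bias.

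**4. Can the death rule change the conclusion?** A simulation used gamma-distributed stay (mean 7, SD 4 days), the same in both arms, with deaths falling at 0.5 to 2.5 days, 20 per arm and 40,000 runs.

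- No deaths: UF has the shorter mean stay in 50.5% of runs, as it should.
- 10% early deaths with UF, 0% in control: mean stay is 0.56 day shorter with UF, which looks better in 67% of runs. With deaths ranked worst (set to 30 days), the median difference is 0.58 day against UF.
- 5% against 0%: mean stay is 0.29 day shorter with UF. With deaths ranked worst, the median difference is 0.26 day against UF.

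The excess deaths were placed in the UF arm for illustration; placed in control, they would favour control.

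**5. The alternative measure.** On days alive and outside the unit to day 30, a patient who dies in the unit without having left it scores 0. A survivor with one 6-day stay from enrolment scores 30 − 6 = 24, and one with a 10-day stay scores 30 − 10 = 20. The ordering is now the right way round.

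**The case against.** The strongest objection is that the article does not say a death counts as a short stay. It gives only the name of the outcome, and how deaths are handled for one secondary item may be set out in a full protocol or analysis plan that is not shown. That stands in part: it would be wrong to say the plan adopts such a rule. But the choice of a plain duration, and of a death window that starts at discharge, are both stated in the text, and together they leave the gap.

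A reader might also infer that UF is expected to cause many deaths here, since the Background reports high in-hospital mortality with UF. The article does not support that. The report concerns patients refractory to standard medical therapy, whereas this trial treats within 24 hours of admission and excludes several high-risk groups. The citation makes in-hospital death a reasonable thing to plan for; it supplies no rate.

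A third tempting inference is that the comparison is biased whenever someone dies. It is not: similar early unit deaths in both arms would largely cancel.

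Finally, little rests on this outcome. It is secondary, summarised descriptively, and outside the primary endpoint. Adverse events are recorded, so a unit death would be known to the investigators. These points limit the weight of the concern but do not remove it.

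**Conclusion.** The concern holds in a limited form. As worded, unit stay ends at death and shorter reads as better, while the listed mortality outcome, taken literally, starts too late to show a death in the unit. If early unit deaths are unbalanced, the arm with more of them gains about 0.2 to 0.4 day of mean stay per excess death. This assumes death at 2.5 days, a stay of 6 to 10 days otherwise, and 20 patients per arm.

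That is small against the sampling error, but with a modest true effect it could decide which arm appears to have the shorter stay. The documents do not support saying that the trial will be biased towards UF, that it has adopted a rule counting deaths as short stays, or that its primary conclusions are at risk. The outcome pair is worth correcting.

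**What to change.** - **Replace the analysed outcome** with days alive and outside CCU/ICU from enrolment to day 30 after enrolment. Days after death count as zero, so a death in the unit scores only days already lived outside it. Compare the arms with a two-sample rank test and report the Hodges-Lehmann difference with its 95% CI.
- **Keep raw CCU/ICU stay** as a descriptive figure, always shown beside the number of unit deaths in each arm.
- **Count all-cause and cardiovascular death from enrolment**, including in-hospital deaths, through the existing visit 30 days after discharge.

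No extra visit is needed: that visit falls on or after day 30 from enrolment for every survivor. There is a small data cost. CCU/ICU days in any readmission before day 30, whatever the cause, must be recorded at that visit, and the listed outcomes capture only heart failure rehospitalisations. The new measure is less familiar and mixes mortality with resource use, which is why raw stay should still be shown. Recruitment began in December 2018 and the trial is open-label, so the change should be dated and made before anyone compares outcomes by arm.
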